### Randomization

Participants who meet the study inclusion criteria will be randomly assigned to receive one of the two conditions. Fig 3 shows the way that participants will flow through the three assessment points for the study (Time 1, T1; Time 2, T2, Time 3, T3). Randomization will occur during T1, immediately after the data collection of psychological measures. The participants will not be informed of the condition to which they have been allocated.

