### Blinding

Participants will not know the treatment group to which they have been assigned. Personnel who interact directly with the study subjects will not be aware of the assigned treatments (i.e., double-blinded). Personnel who analyze the data collected from the study will be aware of the treatment applied to the given groups; however, they will not interact directly with the participants to ensure double-blindness.

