### Sampling plan

According to the registry of the Division of Cancer Prevention and Genetics (IEO), all women with *BRCA1* and/or *BRCA2* germline mutations with at least a male relative will be reached by a phone call and/or an email. During the first contact, a member of the research team informs the female patients about the research purposes and the procedure. The researcher will then ask the women to share the information with their male relative(s) and to invite him (them) to participate in the research. All the information about the research, including an invitation letter, an information sheet, and the consent form, will be also sent by email to the women. If those relatives want to be contacted to participate in the study, a researcher calls them and shares with them the information sheet, the informed consent, and the link to the online survey (via Qualtrics^TM^ Platform). Self-referral of the male participants who have been told by their female relatives about the study will be considered as well. Participants will sign the informed consent before starting to fill the survey and data collection will be done through an online survey via the use of an identifier. Table 1 shows inclusion and exclusion criteria.

**Table 1 pone.0266327.t001:** Inclusion and exclusion criteria for the male participants.

Inclusion criteria	Exclusion criteria
Male relatives of patients with an established germline genetic mutation (pathogenic or likely pathogenic variants) of the BRCA1 and / or BRCA2 genes	*BRCA1* and / or *BRCA2* germline genetic screening load detected
Aged ≥ 18	Diagnosis of breast, pancreatic, or prostate cancer
Able to give informed consent	
Able to read, speak, and understand Italian	

Note: ^a^ = this criterion was not present in the study protocol approved by the Ethical Committee.

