#### Intervention

Participants will be randomly assigned to two groups. Both groups receive a message in which the main character is a man who speaks in first-person. The character has a sister with a *BRCA* germline mutation. After this common introduction, the content of the messages becomes different.

Group 1 receives a self-referred narrative message in which the protagonist explains that he has decided to have a genetic test to discover BRCA germline mutation. He then explains the reasons why this decision is important to himself (e.g., implementing preventive behaviors) and what are the possible benefits for the individual (S1 Fig 1 in S1 File).

Group 2 receives a family-referred narrative message in which the frame is similar to the previous message, but the character this time explains what the benefits for his family are and why his decision to have a genetic test is important to them (S1 Fig 2 in S1 File).

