#### Time 2 assessment

The original study protocol approved by the Ethical Committee included a T2 assessment with questions on intention to undergo germline genetic testing and evaluation of the quality of the message content, and a subsequent (3–4 weeks later) T3 with coping self-efficacy, action planning, and coping planning. Since the HAPA model does not state that there should be a waiting time between the measurement of the intention and the coping/action planning, we collapse T2 and T3. Therefore, one-two weeks after the administration of T1, via an online survey, participants reply to questions on intention to undergo germline genetic testing, coping self-efficacy, action planning, and coping planning.

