### Primary and secondary outcomes

The primary objective of the present research project is to compare self-referred message to family-referred message promoting men’s adherence to evidence-based guidelines on *BRCA1/2* germline genetic testing. The primary clinical objective is to determine what is the best communication strategy to inform men who are at risk to have a germline mutation because they are relatives of women with such a mutation. The primary hypothesis of the study is that family-referred narrative gain framed message (vs. self-referred narrative gain framed message) will produce greater intention and action to undergo genetic testing for *BRCA 1/2* germline mutations in at-risk men.

The secondary objective is to assess men’s characteristics (demographic information, psychological characteristics, health status) that may explain the intention and the action to undergo genetic test for BRCA germline mutations.

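### Men are randomised individually although several may come from one family, so relatives can receive different messages and the primary comparison (HP5) can be diluted to an unknown extent

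*Protocol article*

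**What the plan says.** **Unit of allocation.** Under Randomization: "Participants who meet the study inclusion criteria will be randomly assigned to receive one of the two conditions". This happens during T1, after the psychological measures. No section names the family or the index woman as a unit.

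**Recruitment.** Under Sampling plan, the researcher is to "ask the women to share the information with their male relative(s) and to invite him (them) to participate in the research". The article adds: "Self-referral of the male participants who have been told by their female relatives about the study will be considered as well". More than one man per woman is therefore expected, and news of the study travels by family conversation.

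**Messages.** Both open in the same way. Then: "After this common introduction, the content of the messages becomes different". In the family-referred version the character "explains what the benefits for his family are and why his decision to have a genetic test is important to them".

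**Blinding.** "Participants will not know the treatment group to which they have been assigned".

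**Outcomes and timing.** The primary hypothesis is that the family-referred message "will produce greater intention and action to undergo genetic testing for" BRCA1/2 mutations. Intention is measured "one-two weeks after the administration of T1, via an online survey". Action is collected from the end of T2 for three months.

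**Analysis.** HP5 is tested by ANCOVA, and message is the only predictor listed for it.

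**The concern.** A trial of messages needs each man's outcome to reflect the message he was given. Here brothers, or a father and son, can both enrol, read different texts and have weeks to months to talk before either primary outcome is recorded. The article's own introduction gives reason to expect such talk: it cites qualitative work in which men's decisions to be tested were shaped by felt obligations to family, and one of the two messages is built on that idea.

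If relatives pass on what they read, each arm receives part of the other arm's message and the contrast shrinks. If a man in the self-referred arm is tested because a relative in the family-referred arm urged him, his test counts for the self-referred message. A null HP5 result would then be hard to read: the focus of the message may not matter, or the arms may have been mixed. Cluster-robust errors alone would not cure this. They correct the standard error, whereas interference changes the quantity being estimated.

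The participant blind is affected more narrowly. Men who compare texts may learn that a second version exists and which one they had.

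**Working it through.** **1. How often families would be split.** With simple 1:1 individual allocation, the probability that m men of one family do not all get the same message is 1 − 2 × 0.5^m = 1 − 0.5^(m−1). This gives 50% for m = 2 and 75% for m = 3. The article does not give the distribution of m.

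**2. The plan's own sample size.** Inputs from Sample size and power calculation: partial η² = .05, alpha .05, power .70, two groups, seven covariates, stated result 132 (66 per group), enrolment 264.
- f² = .05/.95 = 0.0526, so f = 0.229 and d = 2f = 0.459.
- Test: F with df1 = 1, df2 = N − 2 − 7, noncentrality λ = N f².
- These inputs give N = 120 for power .70, so 132 is not reproduced. Power is 0.74 at N = 132 (λ = 6.95) and 0.96 at N = 264 (λ = 13.89). The mismatch is a separate matter and the present point does not depend on it.

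**3. Effect of losing part of the contrast.** Let c be the share of the contrast lost (an assumption). Then d becomes d(1 − c) and λ becomes N f² (1 − c)².

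| c (assumed) | Power, N = 132 | Power, N = 264 | N for power .70 |
|---|---|---|---|
| 0 | 0.74 | 0.96 | 120 |
| 5% | 0.70 | 0.94 | 132 |
| 10% | 0.65 | 0.92 | 147 |
| 20% | 0.55 | 0.84 | 186 |
| 30% | 0.45 | 0.74 | 242 |

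**4. What c stands for.** Suppose a share e of men has a relative in the other arm, and each such man, in both arms, moves a fraction s of the way towards the other message. Among them the contrast is d(1 − 2s), so overall c = 2se. If half of all men are exposed, c runs from 0 (s = 0) to 50% (s = 0.5, no contrast left among exposed men). If a share q of men comes from two-man families and the rest enrol alone, e = q/2; with s = 0.5, c = q/2, so the rows for 5, 10, 20 and 30% correspond to q = 10, 20, 40 and 60%. Neither q nor s can be taken from the article.

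**5. Cost of allocating by family.** Design effect = 1 + (m − 1) × ICC. With an assumed 1.5 to 2 men per family and ICC 0.05 to 0.3, it runs from 1 + 0.5 × 0.05 = 1.025 to 1 + 1 × 0.3 = 1.30. The equivalent of 132 becomes 136 to 172, and of 264 becomes 271 to 344. If enrolment stays at 264, power is 0.96 to 0.90.

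**The case against.** The strongest reply is that the article shows a possibility and not an event. It does not say how many women bring in more than one man, or that men share what they read. It condenses a longer protocol, and the flowchart is not visible here. If nearly every woman brings one man, the effect is small. This stands as a limit on size. It does not remove the point, because the article itself states that participants are the unit assigned and that a woman may invite several.

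On size, enrolment of 264 keeps power above the plan's .70 even at a 30% loss. That is correct. Dilution would still bias the estimated difference towards zero, whatever the power.

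On direction, prompting that is equally strong from both arms and simply adds to a man's own response need not shrink the contrast. This also stands. Dilution is clearest where the messages themselves are passed on. It can also arise for action, which is yes or no: a man already persuaded by a relative cannot be moved further by his own message. A reader might also infer that one man's test result, by changing a relative's reason to be tested, adds to the dilution. It could equally widen the contrast, so it does not support the point.

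On blinding, the message is shown inside an online survey and nothing says that men keep a copy. The information sheet is not shown either, so what men already know about a second version is unknown. The risk is real only for men who do compare, and it bears mainly on self-reported intention.

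**Conclusion.** The concern holds as a design weakness: individual allocation combined with recruitment of several men per family allows the two arms to mix before both primary outcomes are measured, and the article describes no safeguard. The HP5 contrast can be diluted. A reader might infer that it will be, or that one particular percentage of the effect is lost with a fixed inflation of the sample size. The article supports neither, because men per family and the degree of sharing are not given and the same exposure can produce very different losses.

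What can be said is conditional. At N = 132 a loss of 5% already uses up the margin above the planned .70; at N = 264 power falls to 0.84 with a 20% loss and to 0.74 with a 30% loss. These figures rest on partial η² = .05 and an F test, so they speak to intention. The power calculation does not cover action as a yes/no outcome, and action has the longer window for spillover.

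**What to change.** - **Allocation.** Link each man, including those who refer themselves, to his index woman's identifier. Allocate the message once per index woman's family by concealed computer allocation in the survey platform, so that all her male relatives receive the same message. Where two women in the registry belong to one family, give them one family number.
- **Analysis.** Analyse HP5 with family as the cluster, by a mixed model or cluster-robust errors.
- **Recruitment.** Have each woman's invitation go to all her relatives before any man sees a message, and report men enrolled per family by arm.
- **Families already split.** Record family links, and run a sensitivity analysis restricted to families with one enrolled man or with all men in the same arm. It is supportive only, since the number of men who enrol may itself depend on the message. Using only the first man per family would not serve: he can still be influenced by a later relative in the other arm.

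**Costs.** The work is an allocation rule in the platform, a linking field and a short protocol amendment. Precision falls slightly in multi-man families (design effect about 1.03 to 1.30 under the assumptions above) and not at all in one-man families. Arm sizes may differ slightly. HP5 would then estimate the effect of a message including reinforcement within the family, and the protocol should say so. Later relatives may be recruited differently by arm, because a man who has read one message may bring in more relatives. The early invitation limits this but does not exclude it.

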**Fig 3 pone.0266327.g003:**
[figure not shown]
Flowchart of the RCT.

#### Time 1 assessment

All participants will complete the T1 assessment, via an online survey which will be available for a two-week period. The T1 measures will include demographic, health status, risk perception, health risk aversion, and intolerance of uncertainty. After this evaluation, participants will be randomized and exposed to one message. A manipulation check, the evaluation of the perceived quality of the information presented on the messages, positive outcome expectations, action self-efficacy, benefit for genetic test will be then collected. The constructs of trust in doctors and health literacy included in the original study protocol approved by the Ethical Committee have been not integrated here.

#### Intervention

Participants will be randomly assigned to two groups. Both groups receive a message in which the main character is a man who speaks in first-person. The character has a sister with a *BRCA* germline mutation. After this common introduction, the content of the messages becomes different.

Group 1 receives a self-referred narrative message in which the protagonist explains that he has decided to have a genetic test to discover BRCA germline mutation. He then explains the reasons why this decision is important to himself (e.g., implementing preventive behaviors) and what are the possible benefits for the individual (S1 Fig 1 in S1 File).

Group 2 receives a family-referred narrative message in which the frame is similar to the previous message, but the character this time explains what the benefits for his family are and why his decision to have a genetic test is important to them (S1 Fig 2 in S1 File).

#### Time 2 assessment

The original study protocol approved by the Ethical Committee included a T2 assessment with questions on intention to undergo germline genetic testing and evaluation of the quality of the message content, and a subsequent (3–4 weeks later) T3 with coping self-efficacy, action planning, and coping planning. Since the HAPA model does not state that there should be a waiting time between the measurement of the intention and the coping/action planning, we collapse T2 and T3. Therefore, one-two weeks after the administration of T1, via an online survey, participants reply to questions on intention to undergo germline genetic testing, coping self-efficacy, action planning, and coping planning.

#### Time 3 assessment

Starting from the end of T2 until 3 months later, data on action initiation will be collected (i.e., genetic test for *BRCA1/2* gene germline mutations).

## Measures

### T1 measures

Before the randomization, all participants answer several questions, as follows.

#### Demographic

Self-reported age, education, occupation, degree of relationship with the woman with *BRCA1/2* genes germline mutation, household composition.

#### Health status

Self-reported general health and existing diagnosis for chronic disease will be investigated with a single item each [53]. Response options for general health conditions will be on a 5-point Likert scale. The response options for the item on the existing chronic disease will be binary coded (no—yes, specify).

#### Risk perception

The risk perception will be evaluated through three different measures. Relative risk perception regarding the possibility to develop breast, prostatic, and pancreatic cancer will be investigated with one item each [54, 55]. Response options are on a 7-point Likert scale. The six items of the Health Risk Attitude [56] will be administered to assess how a person would resolve risky health decisions. Response options are on a 7-point Likert scale. The items of the Intolerance of Uncertainty Scale-12 [57] will be applied to measure two dimensions of the intolerance of ambiguity, which are the desire of predictability and uncertainty paralysis. Response options are on a 5-point Likert scale.

### T2 measures

After the message exposure, participants reply to several questions.

#### Manipulation check

Two items created ad hoc evaluate whether participants have read and understood the message content. Multiple-choice answers are used with one correct answer and two incorrect answers as distractors. Participants who fail to answer those questions will be excluded from the analyses.

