### Statistical analyses

Data exclusion: The answers to the manipulation check will be analyzed before the main analyses to see whether participants have read the message until the end, understood, and recalled the content.

Missing data: presence of missing data will be checked before conducting the main analyses. If a subject does not complete T1 and T2 that subject will be excluded from the analysis.

Normality of the data will be checked before conducting the main analyses. Non-normality will be handled applying either non-parametric tests or SEM with estimator for non-normal distribution.

Statistical analyses will be performed in SPSS version 25 and the *Lavaan* and *SemPaths* packages in RStudio software.

Preliminary analysis: Pearson’s r correlations among variables.

Main analyses: the hypotheses 1, 2, 3, and 4 will be tested either using structural equation modeling (SEM) or multiple regressions. Research question 1 will be tested either using structural equation modeling (SEM) or ANOVA. In case of non-normality in the data, WLSMV will be applied and the Satorra-Bentler scaled test statistic and robust standard errors were used. In the model specification, the factor loading of the first indicator of each latent variable will be set to 1. The following goodness-of-fit indices will be used to evaluate model-data correspondence: the Chi-square value, the Comparative Fit Index (CFI), and the Root Mean Square Error of Approximation (RMSEA). The model will be considered as acceptable when the CFI is higher than .90 and close to .95 and when the RMSEA is .08 or less. Finally, modification indices and the matrix of standardized correlation residuals will be inspected for potential improvement of model fit. Direct, indirect (or mediate), and total effects were also estimated. To test hypothesis number 5 an ANCOVA will be applied.

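### Dropping men who fail the post-message check, or who do not complete T2, removes the protection of randomisation from the primary message comparison (Hypothesis 5)

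*Protocol article*

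**What the plan says.** **Order of events.** The Randomization section states: "Randomization will occur during T1, immediately after the data collection of psychological measures". The Time 1 assessment section agrees: "After this evaluation, participants will be randomized and exposed to one message". The manipulation check is listed there among the items collected after the message. The Measures section lists it under T2 instead. Both places put it after message exposure, and so after allocation.

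**First rule.** Under Manipulation check: "Two items created ad hoc evaluate whether participants have read and understood the message content", and then "Participants who fail to answer those questions will be excluded from the analyses". Statistical analyses puts this step ahead of the hypothesis tests, as an exclusion, and words it so: "The answers to the manipulation check will be analyzed before the main analyses to see whether participants have read the message until the end".

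**Second rule.** Under missing data in Statistical analyses: "If a subject does not complete T1 and T2 that subject will be excluded from the analysis". T2 follows T1 by one to two weeks.

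**Comparison affected.** Primary and secondary outcomes names the family-referred versus self-referred comparison, on intention and action, as the primary hypothesis. Statistical analyses tests it by ANCOVA. No hypothesis is exempted from either rule.

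**Action outcome.** T3 measures ties the recording of action to the appointment and the test itself. Time 3 assessment says: "Starting from the end of T2 until 3 months later, data on action initiation will be collected".

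**The concern.** The check asks about the message that the man was allocated. After a shared introduction the two messages differ in content, so the chance of passing may depend on the arm. T2 completion is also behaviour after allocation. If the men removed differ between arms in engagement, the remaining men differ in intention even when the messages work equally well.

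The likely direction is awkward. If a message is harder to follow, its arm loses more of its less engaged men and those who stay look better, so the weaker message can gain from the rule. The stated objective is to find the best way to inform at-risk men. Whether a message is read and understood is part of how well it does that.

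For action the second rule has a further cost. Whether a man booked and took a test does not depend on his having filled in the T2 survey, yet the rule removes him from the analysis.

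**Working it through.** **1. Do the exclusions follow allocation?** The sequence is baseline scales, randomisation, message, check, then T2 one to two weeks later. Check failure and T2 non-completion therefore both come after randomisation. The exception is a man who leaves T1 before he is randomised; excluding him does no harm.

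**2. Inputs.** The article states no pass rate, completion rate or correlation, so there is no figure of its own on this point to reproduce.
- From the article: 264 men, two arms, hence 264/2 = 132 per arm; design effect partial η² = .05; cited earlier effect η² = .01.
- Assumed: no true message effect; engagement correlates 0.5 with intention and 0.7 with the check score; 90% pass in one arm and 90%, 80% or 70% in the other.

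**3. Selection model.** Intention and a latent check score are bivariate normal with correlation r = 0.5 × 0.7 = 0.35. A man is kept if his check score exceeds a cut c that gives pass rate p. Among those kept, mean intention is r·λ(p), where λ(p) = φ(c)/p, and its variance is 1 − r²λ(λ − c).
- λ(0.90) = 0.1950, λ(0.80) = 0.3500, λ(0.70) = 0.4967.
- Variances: 0.9647, 0.9489, 0.9379.

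**4. Spurious difference,** r × [λ(p₂) − λ(p₁)]:

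| Pass rates | Spurious d |
|---|---|
| 90% vs 90% | 0 |
| 90% vs 80% | 0.35 × 0.1550 = 0.054 |
| 90% vs 70% | 0.35 × 0.3017 = 0.106 |

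With an engagement–intention correlation of 0.3 (r = 0.21), the last two rows become 0.033 and 0.063.

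**5. Type I error,** two-sided 5% test, 132 randomised per arm, t = d/SE:
- 90% vs 80%: SE = √(0.9647/118.8 + 0.9489/105.6) = 0.1308; t = 0.415; Φ(−1.96 + t) + Φ(−1.96 − t) = 7.0%.
- 90% vs 70%: SE = √(0.9647/118.8 + 0.9379/92.4) = 0.1352; t = 0.781; error 12.2%.
- At 66 per arm, the figure in the power calculation, the same steps give 6.0% and 8.6%.

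**6. Scale.** d = 2√(η²/(1 − η²)).
- η² = .05: d = 0.459, so the bias is 0.054/0.459 = 12% to 0.106/0.459 = 23% of the design effect.
- η² = .01: d = 0.201, so the bias is 27% to 53% of the cited effect.

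**7. Precision.** With 264 analysed, two groups and seven covariates, ANCOVA power at η² = .05 is 0.960. With 30% excluded (185 men) it is 0.874. Lost power is not the main issue.

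**The case against.** **The messages look closely matched.** Both are in the first person, share an introduction and use a similar frame. The texts are in a supplement not shown here, and the wording of the two check items is not given; the items could even concern the shared introduction. A reader might infer that passing must differ by arm, or that the primary result will be biased. The documents do not support that, and equal 90% retention gives no bias in the model above. What stands is that the plan relies on equal failure without protecting itself against unequal failure.

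**The numbers are assumed.** This is true. A 90% vs 70% gap is large for two matched stories, and against the effect the trial is designed for the bias is modest.

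**Intention exists only at T2.** Men who skip T2 have no intention value under any plan, so for that outcome the second rule is a choice about missing data. The criticism of needless exclusion applies to action only.

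**The action window.** A reader might infer that tests booked between the message and T2 are lost, and that men who never complete T2 have no window at all. Time 3 assessment says when data are collected, not that earlier bookings do not count, and T3 measures ties recording to the appointment and test. The text is unclear on this and shows no such loss.

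**An article leaves detail to the full plan.** Imputation methods and sensitivity sets may well be there. But the two exclusion rules are stated in the article, and the objection is to them.

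**Conclusion.** The point holds. Both rules act on events after allocation and both apply to the primary hypothesis as written, so Hypothesis 5 is no longer protected by randomisation. That the rules exist and come after randomisation is certain for the check. For T2 completion it rests on reading the second rule as requiring both T1 and T2; read as missing both, it would exclude fewer men. Whether failing the check means a wrong answer or a blank one is also open, but either follows allocation.

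The size is conditional on the assumptions in the working. It is zero if exclusion and its reasons are alike in the two arms, and otherwise a bias that is modest against the design effect but a quarter to a half of the effect the article itself cites. Hypotheses 1 to 4 and Research question 1 are not randomised comparisons and are less affected.

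**What to change.** - Define the primary Hypothesis 5 analysis as all randomised men in their assigned arm, whatever their answers to the manipulation check.
- Analyse action for every randomised man, whether or not he completed T2. State that action is counted from randomisation over one fixed window, the same for all men, so that bookings made before T2 have a clear place.
- Handle missing T2 intention by a stated method, for example multiple imputation from the T1 variables and arm.
- Report check-passers, and completers of both T1 and T2, as sensitivity analyses.
- Say whether failing the check means a wrong or a blank answer, and whether the completion rule is triggered by missing either assessment or both.

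The cost is wording and one imputation step. The message contrast will be slightly diluted by men who did not read their message, but the passers-only result is still reported beside it.
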